## Research questions and hypotheses

Our main research question is whether cognitive behavioural therapy, CBT, is effective treatment for CFS/ME, this can be divided into 2:

- 1) Does cognitive behavioural therapy improve physical function, fatigue and psychological issues in patients diagnosed with CFS/ME?
- 2) Is short cognitive behavioural therapy, I-CBT, equal to or better than standard, long CBT intervention in treatment of CFS/ME?

## Hypothesis

(1) Standard CBT (CBT) and short CBT (I-CBT) are significantly better compared to the waiting list control group (WLC) in the primary outcome measure physical function in SF-36 and in the secondary outcome measures fatigue and the rest of the SF-36 subdimensions.

(2) There is no difference in effect between I-CBT and standard CBT in the primary outcome measure physical function in SF-36 and in the secondary outcome measures fatigue and the rest of the SF-36 subdimensions.

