## Is cognitive behavioural therapy a good treatment for chronic fatigue syndrome?

### Summary:

The Norwegian Directorate of Health has requested documentation on treatment for chronic fatigue syndrome, CFS/ME. With this trial, The National Competence Centre for Complex Symptom Disorders (NKSL) wants to contribute to knowledge on whether cognitive behavioural therapy is good treatment for CFS/ME. Even though standard, individual CBT together with graded exercise therapy so far is the best documented treatment, there is no national or international consensus due to few randomised trials, varying quality and moderate evidence. Therefore, our goal is to test the effect of individual standard CBT, in a randomized, controlled 1-year follow-up trial. Our second goal will be to test the effect of a newly developed and shorter individual CBT (I-CBT). If the shorter therapy turns out to be as good as or better than standard CBT, the shorter therapy will be an equal and more cost-effective treatment. Patients with nonspecific fatigue will undergo a thorough, multidisciplinary assessment at the The Department for Pain and Complex Symptom Disorders (ASSL), St. Olav`s Hospital, to be diagnosed with CFS/ME or other fatigue conditions. Patients diagnosed with CFS/ME will be offered treatment in our trial with randomisation to either short I-CBT or standard individual cognitive behavioural therapy or a control group. Primary outcome measures are physical function, health related quality of life and fatigue. NKSL is a research group at ASSL, St. Olav`s Hospital that wants research to be the basis for the operation of its three outpatient clinics; the clinic for pain, the clinic for CFS/ME and the clinic for assessment to work related rehabilitation at Hysnes, Norway.

In our opinion, this study fits perfectly with the announcement:

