#### *Analyses:*

Calculation of sample size and power. We have calculated sample size assuming a mean change in SF-36 score of 10, 5, and 0 from baseline of respectively short I-CBT, standard CBT, and WLC group, a ‘within cell’ standard deviation (SD) on 15 and a correlation between baseline and post score on 0.3 (r-squared on 0.1). For a two-sided test with 5 % significance level and 80 % power, we calculated that we needed 40 patients in each group, 120 in total. Assuming a maximum drop-out level of 25 %, we calculated that we needed an additional number of 18 patients in each group, 174 patients in total. A mean change in SF-36 score of 10, 10, and 0 for short, standard, and WLC groups would increase power to 90 %.

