### Statistical analyses:

ANCOVA and "mixed random effects regression" will be used to compare the post-score / outcome variables in the three intervention cohorts (among others physical function in SF36). All analyzes will be adjusted for baseline scores with postscore as outcome variables. The three intervention cohorts will be compared at X, Y and Z months. We will perform separate analyzes for each follow-up time (ANCOVA) as well as combined analyzes for all times (mixed random effects regression). The results will be presented as "least-squares means with standard errors (SE). Differences between cohorts will be reported with 95% confidence interval (CI).

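### The stated 80% and 90% power belong to a three-group test, but the first goal and hypothesis 1 rest on comparisons with the waiting list that have about 34% and 33% power under the plan's own base case

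*Protocol*

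**What the plan says.** Five places in the protocol bear on which comparison decides whether CBT works on the primary outcome, SF-36 physical function.

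- **Summary:** "our goal is to test the effect of individual standard CBT, in a randomized, controlled 1-year follow-up trial". The effect of the shorter I-CBT is named as a second goal.
- **Research questions and hypotheses:** "Our main research question is whether cognitive behavioural therapy, CBT, is effective treatment for CFS/ME". The question is general and names neither a therapy arm nor a comparator.
- **Hypothesis (1):** "Standard CBT (CBT) and short CBT (I-CBT) are significantly better compared to the waiting list control group (WLC"). The two therapies are joined by *and*.
- **Analyses (sample size and power):** the inputs are a "mean change in SF-36 score of 10, 5, and 0 from baseline of respectively short I-CBT, standard CBT, and WLC group", a within-cell SD of 15 and a baseline to post-score correlation of 0.3. "For a two-sided test with 5 % significance level and 80 % power, we calculated that we needed 40 patients in each group". Also: "A mean change in SF-36 score of 10, 10, and 0 for short, standard, and WLC groups would increase power to 90" per cent.
- **Statistical analyses:** the three cohorts are compared with adjustment for baseline, and "Differences between cohorts will be reported with 95% confidence interval (CI"). No deciding comparison is named.

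The control group is scored after 16 weeks of waiting and is then offered I-CBT outside the study (Intervention, control group).

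**The concern.** The Summary points to standard CBT against the waiting list, hypothesis 1 to both therapies against the waiting list, and the sample size to a single test across three means. These are different targets with very different chances of success.

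A reader of the power statement will take 80% as the chance of confirming what the trial sets out to show. If it belongs to a test that answers neither the first goal nor hypothesis 1, the trial is much weaker for its stated aims than it appears. A significant three-group test also does not say which therapy works. If the base-case assumption is true, a frequent outcome is that I-CBT beats the waiting list and standard CBT does not. Hypothesis 1 would then fail and the first goal would not be shown, yet the three-group test would usually be significant.

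**Working it through.** **Inputs, all from the sample size paragraph.** SD 15; correlation 0.3, so r² = 0.09 (the protocol rounds to 0.1); 40 per group; two-sided 5%; mean changes 10/5/0 or 10/10/0 for I-CBT, standard CBT and waiting list (WLC).

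Residual variance after baseline adjustment: 15² × (1 − 0.09) = 204.75, SD 14.31. Error df: 120 − 3 − 1 = 116.

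**Step 1: reproduce the plan's power with a three-group test (2 numerator df).** Noncentrality λ = n × Σ(mean − grand mean)² / residual variance; critical F(2, 116) = 3.07.

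- 10/5/0: Σ = 25 + 0 + 25 = 50; λ = 40 × 50 / 204.75 = 9.77; power **79.5%** (80.0% with r² = 0.1).
- 10/10/0: Σ = 11.11 + 11.11 + 44.44 = 66.67; λ = 40 × 66.67 / 204.75 = 13.02; power **90.1%** (90.4% with r² = 0.1).

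Both stated figures are recovered.

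**Step 2: try pairwise sizing.** n per arm = 2 × (1.96 + 0.84)² × 204.75 / Δ². For Δ = 10 this gives 32.1, so 33; for Δ = 5 it gives 128.6, so 129. Neither is 40. Splitting alpha over two tests gives 39 for Δ = 10. But the power of a 10-point comparison does not depend on the third group's mean, so it cannot explain the rise to 90% when standard CBT moves from 5 to 10.

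**Step 3: power of the comparisons that the goals and hypothesis 1 name.** The SE of a difference is 14.31 × √(2/40) = 3.20 and the critical t is 1.98. Noncentrality is 10/3.20 = 3.13 for a 10-point effect (power 87%) and 5/3.20 = 1.56 for a 5-point effect (power 34%). The joint results below come from simulation with the shared control group.

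| Result at 40 per group | 10/5/0 | 10/10/0 |
|---|---|---|
| Three-group test significant | 79.5% | 90.1% |
| I-CBT beats WLC | 87% | 87% |
| Standard CBT beats WLC (Summary, first goal) | 34% | 87% |
| Both beat WLC (hypothesis 1 as worded) | 33% | 79% |
| I-CBT beats WLC, standard CBT does not | 54% | 8% |

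**Step 4: type I error with no true effect.** The two comparisons share a control group of equal size, so they correlate at 0.5.

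- Both must win: about 0.5% in the direction of benefit. If one therapy works and the other does not, it is at most 2.5%. There is no inflation.
- Either may win, each tested at two-sided 5%: 5% + 5% − 0.93% (both significant) = 9.07%. In the direction of benefit: 2.5% + 2.5% − 0.46% = 4.54%, against a nominal 2.5%.

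**Step 5: three-group test first, then each therapy against WLC at 5%.** With no true effect, the chance of a significant result for either therapy is about 4.1%. With changes 10/0/0, the chance of a significant result for standard CBT is 4.95%. Power under 10/5/0 is 79% for I-CBT and 33% for standard CBT.

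**The case against.** A reader might infer that the plan tests at 9% rather than 5%. The protocol does not support that. Hypothesis 1 says *and*, no section lets either therapy alone carry the claim, and the 9% includes trials in which a therapy is significantly worse than waiting. A rule for multiple comparisons may also stand in a SAP that is not at hand, so its absence from the protocol is no fault in itself.

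Nor are there three contradictory questions. The general research question names no arm, and the hypothesis directly below makes it specific. The Summary lists both therapies, and listing one first is not a declared testing order.

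The 10/5/0 case is not the only one considered. Under 10/10/0, standard CBT has 87% power and the split result occurs in about 8% of trials.

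These points stand, and they remove the error-rate claim as a finding. They do not remove the mismatch in power. The 10/5/0 case is the one that fixes the 40 per group. Under 10/10/0 the power for hypothesis 1 is still about 79%, not the stated 90%. Recruiting above 40 helps little: even if all 58 per group were analysed, the SE would be 14.31 × √(2/58) = 2.66, and power for a 5-point effect would be about 47% (normal approximation: 5/2.66 − 1.96 = −0.08).

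**Conclusion.** The point holds as a mismatch between the power statement and the stated aims. The 80% and 90% describe a three-group test. Under 10/5/0 at 40 per group, they do not apply to hypothesis 1 as worded (about 33%) or to standard CBT against the waiting list (about 34%); under 10/10/0, hypothesis 1 has about 79%.

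This rests on the plan's own means, SD, correlation and 40 evaluable patients per group, and on reading the SD of 15 as the value before baseline adjustment. Without that adjustment the three-group test gives 75.4% and 87.0%, so the stated figures would not be recovered.

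The 9% error is conditional on an either-therapy rule that the protocol leaves open but does not state. It is a reason to write the rule down, not an error in the plan as worded.

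**What to change.** In Hypothesis, Analyses and Statistical analyses, state one decision rule for SF-36 physical function at the 16-week score of the control group:

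1. Baseline-adjusted three-group test at two-sided 5%.
2. Only if it is significant, I-CBT against WLC and standard CBT against WLC, each at two-sided 5%.
3. Efficacy claimed only for a therapy whose own comparison is significant in its favour.

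With three arms this keeps the error for the two waiting-list comparisons within 5%. If all means are equal, the first step protects; if only one therapy equals the waiting list, a single true null hypothesis is left, tested at 5%.

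Reword hypothesis 1 and the goals in the Summary to match. Restate power under 10/5/0 as about 80% for the three-group test, 79% for I-CBT and 33% for standard CBT.

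**Cost:** no extra patients or data. It is more than an edit of wording, because hypothesis 1 becomes two per-therapy claims. Power for I-CBT falls from 87% to 79%, power for standard CBT moves from 34% to 33%, and the low power for standard CBT becomes visible. A fixed testing order, a Dunnett-type rule, or an explicit requirement that both therapies win would also settle the matter, provided that power is restated for the rule chosen. Keeping the both-must-win hypothesis means stating about 33% under 10/5/0.

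### Short versus standard CBT is a non-inferiority question, but hypothesis 2 is worded as no difference, without a margin, so an imprecise result could be taken as equality

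*Protocol*

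**What the plan says.** - **Question.** Under Research questions and hypotheses, the second question is: "Is short cognitive behavioural therapy, I-CBT, equal to or better than standard, long CBT intervention in treatment of CFS/ME".
- **Hypothesis.** Hypothesis (2) turns this into "There is no difference in effect between I-CBT and standard CBT in the primary outcome measure physical function in SF-36", and extends it to fatigue and the other SF-36 subdimensions.
- **Conclusion drawn from it.** If the short therapy does as well or better, the Summary says that "the shorter therapy will be an equal and more cost-effective treatment".
- **Sample size.** Under Analyses the calculation is "For a two-sided test with 5 % significance level and 80 % power", with "a mean change in SF-36 score of 10, 5, and 0 from baseline of respectively short I-CBT, standard CBT, and WLC group", SD 15 and a baseline correlation of 0.3. This gives 40 per group, raised to 58 per group for drop-out. A second scenario follows: "A mean change in SF-36 score of 10, 10, and 0 for short, standard, and WLC groups would increase power to 90" per cent.
- **Analysis.** Statistical analyses plans ANCOVA and mixed models, with differences between groups given with 95% CIs. It sets no bound against which to judge the CI for short versus standard CBT.
- **Margin.** None appears. The 10-point figure under Primary outcome measure is a success criterion for improvement, not a tolerated difference between two active arms.

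**The concern.** Equal-or-better is a one-sided claim that the short therapy is not worse by more than some tolerable amount. Written as no difference, it becomes the null hypothesis of an ordinary two-sided test, and such a null is easier to retain the noisier the data are. Without a margin, nothing in the protocol separates a result that shows the arms to be close from one that shows little at all.

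The planning assumptions do not help. The main scenario has the two CBT arms 5 points apart, which conflicts with hypothesis 2. The second scenario agrees with hypothesis 2, but its 90% is power to find a difference among three groups, not power to show two of them alike.

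At stake is the practice conclusion that eight weekly sessions can replace sixteen. The comparison is not a side issue. The waiting-list group is offered I-CBT after 16 weeks, so for the rest of the one-year follow-up short versus standard is the only randomised comparison left.

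**Working it through.** **Inputs (Protocol, Analyses).** SD 15; baseline correlation 0.3 (r-squared 0.09, which the protocol rounds to 0.1); two-sided 5%; 40 per group; 58 per group enrolled; maximum drop-out 25%.

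**1. The protocol's own figures.** The test behind the 40 per group is not named. I took the three-group ANCOVA F test with residual variance 15² × (1 − 0.1) = 202.5, degrees of freedom 2 and 3 × 40 − 4 = 116, and noncentrality n × Σ(mean − grand mean)² / 202.5.
- 10/5/0: 40 × 50 / 202.5 = 9.88, power 0.7995 (stated 80%).
- 10/10/0: 40 × 66.67 / 202.5 = 13.17, power 0.904 (stated 90%).

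Both reproduce. A pairwise reading does not fit: a single 10-point contrast at 40 per arm has about 87 to 88% power, and a single 5-point contrast would need 128 per arm. The stated size therefore powers the overall comparison and says nothing about short versus standard.

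**2. Precision of short versus standard.** Residual SD = 15 × √(1 − 0.09) = 14.31. SE = 14.31 × √(2/40) = 3.20. With t(0.975, 116) = 1.98, the half-width is 1.98 × 3.20 = 6.3 points. An estimate of zero would have a CI of about −6.3 to +6.3, which still includes a 5-point deficit.

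**3. Chance of p>0.05 when I-CBT is truly worse.** Approximately 1 − Φ(deficit/SE − 1.98), at 40 per arm:

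| True deficit of I-CBT | P(p>0.05) |
|---|---|
| 5 points | 66% |
| 7.5 points | 36% |
| 10 points | 13% |

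For the 5-point deficit, 5/3.20 = 1.56 and 1 − Φ(−0.42) = 0.66. With all 58 per arm analysed (no drop-out) it is still 53 to 54%, the range covering r-squared 0.10 and 0.09.

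**4. Power for non-inferiority.** Approximately Φ((margin + true difference)/SE − 1.98), one-sided 2.5%, 40 per arm. The margins are my assumptions.

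| Margin | Arms truly equal | I-CBT truly 5 points better |
|---|---|---|
| 2.5 points | 12% | 64% |
| 5 points | 34% | 87% |
| 7.5 points | 64% | above 95% |
| 10 points | 87% | above 99% |

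**5. Size needed if the arms are equal.** For 80% power, n per arm = 2 × 202.5 × (1.96 + 0.84)² / margin². At 5 points this gives 128 completers. At 2.5 points it is four times as many, about 509.

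**The case against.** Three stronger readings are tempting, and the protocol does not support them.

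- **That a non-significant result will be declared equality.** No decision rule for hypothesis 2 is written down. The planned 95% CIs are exactly what a non-inferiority reading needs once a margin exists. What stands is that the wording leaves this misreading open and the Summary attaches a practice claim to it.
- **That the trial cannot show the short therapy to be as good.** This depends on the margin and the truth. Under the protocol's main assumption, with I-CBT 5 points better, power at a 5-point margin is 87%. The low figures apply when the arms are equal, which is what hypothesis 2 states.
- **That a clearly worse short therapy would usually pass as equal.** This fails for larger deficits: 36% at 7.5 points and 13% at 10. The 66% belongs to a 5-point deficit, in the opposite direction to the gap assumed in the sample size.

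A 5-point margin might also be inferred as half of the 10-point success criterion. It should not be adopted. It equals the whole benefit assumed for standard CBT over waiting list (5 versus 0), so it would preserve none of that benefit. A 10-point margin is twice it.

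A SAP may exist and could hold an interpretation rule. It would not reconcile the question, hypothesis and sample size as the protocol now states them, and a margin belongs with the hypothesis. Hypothesis 1, against the waiting list, is unaffected.

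**Conclusion.** The concern holds as a mismatch between question, hypothesis and sample size on the trial's second aim. The conclusion sought is non-inferiority, the hypothesis is a difference-test null without a margin, and the stated power belongs to a three-group test. Failure to find a difference would be weak evidence of similarity: a deficit equal to the entire benefit assumed for standard CBT would go undetected in about two trials out of three.

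These figures rest on the protocol's SD of 15 and correlation of 0.3, on 40 completers per arm and on a single time point. Using r-squared 0.10 in place of 0.09 changes them by a percentage point or less. It is an inference, though a close one, that the sample size came from the overall F test, since the protocol does not name the test.

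**What to change.** Before the data are analysed, restate hypothesis 2 along these lines: I-CBT is non-inferior to standard CBT on SF-36 physical function if the lower limit of the two-sided 95% CI for I-CBT minus standard CBT lies above minus the margin. Then:

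1. Pre-specify and justify the margin. It should be smaller than the 5-point effect assumed for standard CBT over waiting list.
2. State the power at that margin. With 40 per arm and equal arms it is about 34% even at 5 points and about 12% at 2.5.
3. Report a CI that crosses the margin as inconclusive, not as no difference.

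If no margin can be justified, drop the equality conclusion from the Summary, label the comparison exploratory, and report the estimate with its CI.

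The cost is wording and one pre-specified number. The planned model and CI stay as they are. Recruitment is described as nearly complete, so resizing is not a realistic remedy. The downside is that the comparison may well have to be reported as inconclusive.

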## Secondary research questions

(1) Which baseline factors (beyond the randomised interventions) are associated with physical function and fatigue in the entire CFS/ME selection? (2) Are the intervention effects of CBT for the primary outcome associated with equivalent changes in secondary outcome measures like fatigue, physical fitness, ability to relax, negative affect, pain and number of subjective health complaints? (3) Are the effects of CBT intervention associated with baseline factors like neuropsychological functioning, physical fitness, ability to relax or sociodemographic factors?

## **Design, methods and analysis**

### ***Inclusion and exclusion:***

Patients who meet the diagnostic criteria CFS / ME according to the Fukuda CDC 1994 criteria (1) will be offered inclusion in our treatment study and receive outpatient, individual treatment. Exclusion: Absence of fatigue. Age <18 years and > 62 years. Severe somatic or psychiatric disorder. Pregnancy. Problematic drug use. Poor skills in Norwegian language.

***Design:*** A randomised controlled trial is a suitable design to answer our primary research questions on whether CBT has an effect in CFS/ME. The trial is not blinded for intervention, but the investigator is blinded to measurement of the outcome variables. All the groups will be treated equal during the trial, except from exposure to the interventions that are to be evaluated.

### ***Procedure and patient flow:***

In this project, patients with nonspecific fatigue referred to The Department for Pain and Complex Symptom Disorders (ASSL) St. Olav's Hospital, will undergo a thorough interdisciplinary assessment by a physician and a psychologist, physical tests and blood tests to diagnose CFS / ME and categorize other fatigue conditions. Patients who meet the diagnostic criteria for CFS/ME will, after a neuropsychological test, be randomised to one of three groups in the treatment trial following procedures from the Section for Applied Clinical Research (ACR) at NTNU.

### ***Intervention***

The intervention consists of short (8 weeks) and standard (16 weeks), cognitive behavioural therapy (CBT) that will be compared to a waiting list control group (WCL).

**Figure 1: CFS/ME logistic research project flow chart**

[figure not shown]

**CBT short intervention (I-CBT):** The treatment manual is developed by co-author professor [name]. The intervention consists of eight weekly therapy sessions and a booster session four weeks after the eighth session. The treatment is based on a biopsychosocial model in which elements from interpersonal cognitive therapy and personality-guided therapy are integrated. It assumes that treatment must be individualized to match the prominent personality style of the patient. The patients will be divided into four subtypes: Cautious, achievement oriented, identity or role confused and disease oriented. The overarching goal of the treatment will be to give the patient insight into own personal goals and needs, to know their true inner self, and how to improve their interpersonal relatedness towards others, including family, friends, work relations and health and welfare authorities. The following elements were included in the intervention: ( a ) information and explanation of the CFS symptoms based on contemporary knowledge on both physical and psychological components with specific emphasis on the goals and needs of the self, its ability to emotion regulate and to actively improve relationships with others, ( b ) agreement on long-term goals related to self-satisfaction and interpersonal functioning rather than immediate symptom reduction and increase in physical function, and (c ) focus on individualized personality-guided and interpersonally oriented factors that are assumed to create painful and difficult experiences to the individual. The patient will, in home assignments, test out various types of cognitive techniques and perform various behavioral experiments that are well known in the field of cognitive therapy. During the last two treatment sessions, one will focus on how one can continue what one has learned in the therapy and how to prevent relapse. Supervision in I-CBT will be given by [name] once a month in groups, as well as individually when needed. All treatment sessions will be taped for quality control and guidance.

**Standardised CBT, long intervention:** The intervention consists of 16 weekly sessions plus a booster session four weeks after the 16th session, ad modum "Chalder/Kings College". The actual therapy manual is based on previous manuals from similar trials and associated with the fear avoidance theory (FA) of CFS. The FA theory focuses on the link between cognitive and behavioural responses. The following main elements are included in the intervention: (a) information and explanation of the CFS symptoms based on contemporary knowledge on both physical and psychological components, (b) agreement on goals for the

treatment (c) reading of self-help guides like *Coping with Chronic Fatigue* (d) avoidance of excessive activity or rest and/or sudden change in activity, (e) planning of regular, predictable, continuous activity to prohibit deconditioning, (f) recovering self-confidence and self-control by starting with a five- minute walk morning and night followed by gradual development (GET), and (g) classical CBT-procedures. A treatment manual for SCBT has been developed following [name] guidance. in use at the Division of CFS/ME, Kings College, UK (17). There will be regular supervision of the therapists in relation to this manual. All treatment sessions will be taped which will allow for quality control and satisfactory CBT guidance. Appropriate use of standard CBT will be quality assured using independent observers with CTACS quality assurance instrument afterwards (18) so that all therapists are quality assured as CBT therapists. Guidance is provided by a specialist in CBT guidance (psychiatrist, [name]) regularly once a month in a group, as well as individually when needed.

**Control group (WLC):** The control group is a waiting list control group in which the participants will be asked to wait for 16 weeks after primary assessment and randomisation before they are post-scored and then offered eight weeks of I-CBT outside the study. The ideal would have been a control period up to one year without intervention, but this will not possible due to ethical considerations.

